## Primary endpoint methods

For the primary endpoint, Poisson regression will be used, with number of subjects attending within 90 days of their first offered appointment as the outcome (*90dayattend)*, offset by total numbers invited.

The attendance rate within 90 days of the first offered appointment in the study arms is compared using Poisson regression model with robust variance estimates to take account of clustering in the allocation to arms OI and TA at the first invitation^7^. In STATA the command **poisson** with option **vce(robust)** is used, reporting with 95% confidence interval using **level (95)**, and with option **irr** to output estimated coefficient as incidence-rate ratios.

A likelihood-ratio test is used to check the significance of the regression coefficient in the poisson regression model (STATA **lrtest**). Statistical testing will be two-sided, with p<0.05 considered to be statistically significant. We will compare each of the other groups with the OO group as reference category. Thereafter pairwise comparisons will be carried out as described above. We conclude the following for

- IRR < 1, the attendance rate is decreased for the considered study arm compared to the reference category.
- IRR = 1, no difference between the attendance rate of the considered study arm and the reference category.
- IRR > 1, the attendance rate is increased for the considered study arm compared to the reference category.

The IRR is significantly greater or smaller than 1, if 1 is not within the border of the 95% CI, which is analogue to the p-value is smaller than 0.05.

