**Supplementary Tables**

**Supplementary Table 1**: Breast screening uptake in 2021/22 and Index of Multiple Deprivation (IMD) quintile of selected services determined by the NHSBSP prior to the start of the study

| **Code** | **Service** | **Uptake^a^** | **IMD Quintile^b^** |
| --- | --- | --- | --- |
| FLO | Central and East London | 42% | 3 |
| EBA | North London | 54% | 2 |
| FBH | Outer NE London | 58% | 1 |
| MDU | Dudley, Wolverh. & SW Staffords. | 60% | 2 |
| DCB | Cambridge | 61% | 5 |
| CDO | Doncaster | 63% | 2 |
| LED | North and East Devon | 67% | 4 |
| ^a^ Year 2021/22 figure^3^  ^b^ 1 being the most deprived and 5 being the least deprived.. | | | |

**Supplementary Table 2**: Characteristics of women included in the services evaluation by NHSBSP service.

|  | Service name | | | | | | | | | | | | | |
| --- | --- | --- | --- | --- | --- | --- | --- | --- | --- | --- | --- | --- | --- | --- |
|  | Doncaster | | Cambridge | | North London | | Outer NE London | | Central and East London | | North and East Devon | | Dudley,Wolverh&  SW Staffords ^d^ | |
| Age (Mean, IQR) ^a^ | 60.0 | 54.0 – 65.0 | 54.4 | 50,0-59.0 | 59.4 | 55.0-64.0 | 58.8 | 54.0-64.0 | 58.5 | 54.0.63.0 | 59.1 | 55.0-65.0 | 58.4 | 52.0-64.0 |
|  |  |  |  |  |  |  |  |  |  |  |  |  |  |  |
| IMD (quintile) |  |  |  |  |  |  |  |  |  |  |  |  |  |  |
| 1: most deprived | 628.0 | (23.2%) | 83.0 | (3.6%) | 382.0 | (12.7%) | 1018.0 | (61.1%) | 514.0 | (22.1%) | 199.0 | (8.1%) | 1489.0 | (44.8%) |
| 2 | 422.0 | (15.6%) | 91.0 | (4.0%) | 780.0 | (25.9%) | 619.0 | (37.2%) | 1346.0 | (57.9%) | 306.0 | (12.4%) | 803.0 | (24.2%) |
| 3 | 564.0 | (20.8%) | 356.0 | (15.5%) | 743.0 | (24.7%) | 22.0 | (1.3%) | 304.0 | (13.1%) | 775.0 | (31.4%) | 525.0 | (15.8%) |
| 4 | 719.0 | (26.5%) | 679.0 | (29.5%) | 796.0 | (26.5%) | 2.0 | (0.1%) | 125.0 | (5.4%) | 616.0 | (25.0%) | 426.0 | (12.8%) |
| 5: least deprived | 359.0 | (13.2%) | 1051.0 | (45.7%) | 285.0 | (9.5%) | 0.0 | (0.0%) | 26.0 | (1.1%) | 542.0 | (22.0%) | 73.0 | (2.2%) |
| missing | 18.0 | (0.7%) | 41.0 | (1.8%) | 21.0 | (0.7%) | 4.0 | (0.2%) | 11.0 | (0.5%) | 30.0 | (1.2%) | 9.0 | (0.3%) |
|  |  |  |  |  |  |  |  |  |  |  |  |  |  |  |
| Prevalence and age |  |  |  |  |  |  |  |  |  |  |  |  |  |  |
| prevalent and <60 | 494.0 | (18.2%) | 1556.0 | (67.6%) | 762.0 | (25.3%) | 356.0 | (21.4%) | 805.0 | (34.6%) | 631.0 | (25.6%) | 1015.0 | (30.5%) |

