## Sample Size Justification

We aimed for a sample size of 16,000 women for the following reasons.

Previous results comparing timed to open invitations suggest an absolute 8% increase in participation with timed appointments compared to open invitations. As noted above, there is an interest in subgroup analyses. For a comparison of two groups with participation rates of 65% and 73%, 524 persons per group would give 80% power to detect this difference as significant at 5% level with two-sided testing. To allow for estimation of the primary outcome in socioeconomic and ethnic subgroups, we planned to evaluate 16,000 women in total (4,000 per arm).

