| *imdquintile* | Index of Multiple Deprivation in quintiles | First, small area level index of multiple deprivation 2019 (*imddecile*) by linking *lsoacode (*2011) with IMD2019 data^2^, then derive from deciles to quintiles.   - 1 (least deprived) - 2 - 3 - 4 - 5(most deprived) |
| *ethnicity* | ethnicity (area level estimate) | Small area level ethnicity estimate derived by linking source data with the ethnicity data from Office for National Statistics site^3^ with *lsoacode* as identifier, for women from aged 50 and above, by linking LSOA with census data. Expect in 5 major categories:   - - 1, Asian or Asian British   - 2, Black or Black British   - 3, Mixed   - 4, Other ethnic groups   - 5, White |
| *ethnicity_white* |  | - - Derived from *ethnicity* as defined above.   - 1, white   - 0, non-white |
| *rurality* | Whether the screening site is rural or urban. | Derived by linking source data with the data from open geography portal, on ‘Rural Urban Classification (2011) of Lower Layer Super Output Areas in England and Wales”^4^, using *lsoacode* as identifier.   - - 0, rural   - 1, urban |
| *age_prev_status* |  | Derived from *ageatfoa* and *prevalentincidentstatus:*   - - 1, prevalent and under60,   - 2, incident and under60,   - 3, over60, and   If *prevalentincidentstatus* is missing, impute based on *ageatfoa.* |
| *firstarm* | Open invitation or timed appointment at the first invite. | Derived from *armname* |
| *secondarm* | Open invitation or timed appointment at the second invite. | Derived from *armname* |
| Note: when the *lsoacode* cannot be identified in the sourcedate during data linkage, resolve from checking the data file: LSOA (2011) to LSOA (2021) to Local Authority District (2022) lookup for England and Wales. ^5^ | | |

**NOTE:** The original source dataset should not be altered. Any modification to data extract MUST be saved to a separate file.

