## Primary analysis

For the primary analysis a hierarchical approach will be used for testing at the 5% level. In the first instance, a global likelihood ratio test on 3 degrees of freedom will be applied to assess the significance of a difference in any direction among the groups overall. Also, a four-way comparison with OO as the reference category.

To account for multiple comparisons, null hypotheses (no difference in 90-day screening attendance between arms) will be tested in the following order:

(1) Timed Timed (TT) vs Open Open (OO).

(2) TT vs OT.

(3) TO vs OT.

(4) TT vs TO.

(5) OT vs OO.

Testing will only proceed if the preceding hypothesis was rejected at the 5% level (p-value <0.05).

Independently of significance test results, both overall and for specific subgroups, we will report the most successful group in terms of 90-day attendance.

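### The arm-only primary Poisson model is valid but leaves a little precision unused: service and prevalent/incident-by-age status are already derived and could be adjusted for.

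*SAP*

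**What the plan says.** Under Primary endpoint methods, attendance within 90 days "in the study arms is compared using Poisson regression model with robust variance estimates", with OO as reference. Under Primary analysis, "a global likelihood ratio test on 3 degrees of freedom will be applied", followed by five pairwise tests in fixed order, each made only if the one before it was significant. Three degrees of freedom are what four arms give. This fits a model with arm alone, although it would not by itself rule out covariates. None is named in either section or elsewhere in the SAP.

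The variables that could be used are in the analysis file. Service is created for every record when the extracts are joined (Preparing data for analysis). The three-level variable age_prev_status is built from age at first offered appointment and screening status, with a rule to impute from age when status is missing (Data linkage and variable derivation). Both serve only for description and for subgroup reporting.

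Supplementary Table 1 shows that service is related to uptake. Its lowest entry is "Central and East London | 42% | 3" (uptake, then deprivation quintile), and its highest is North and East Devon at 67%.

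**The concern.** Both variables are fixed before the invitation goes out, so adjusting for them cannot remove any part of the invitation effect. With a log link the rate ratio is collapsible, so under a common ratio the adjusted and unadjusted models estimate the same quantity. Adjustment also takes out chance imbalance in these factors, since the SAP describes no stratification of the odd/even digit allocation.

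Any benefit would fall mainly on the last two steps of the sequence, TT vs TO and OT vs OO. Those arms differ only in the second letter, which reaches only women who did not attend after the first. The sequence is also a gate, so a narrow miss at TT vs TO stops OT vs OO from being tested.

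**Working it through.** **1. The plan's own figure.** For "a comparison of two groups with participation rates of 65% and 73"%, two-sided 5% and 80% power, the pooled-variance formula without continuity correction gives 524 per group. This matches "524 persons per group would give 80% power to detect this difference as significant at 5% level with two-sided testing". At 4,000 per arm, power for that 8-point difference is above 99.9%, so adjustment cannot matter for an effect of that size.

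**2. Service alone.** Sizes are the column totals of Supplementary Table 2; uptakes are from Supplementary Table 1.

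| Service | Women n | Uptake u | n(u − p)² |
|---|---|---|---|
| Doncaster | 2,710 | 0.63 | 6.76 |
| Cambridge | 2,301 | 0.61 | 2.07 |
| North London | 3,007 | 0.54 | 4.82 |
| Outer NE London | 1,665 | 0.58 | 0.00 |
| Central and East London | 2,326 | 0.42 | 59.58 |
| North and East Devon | 2,468 | 0.67 | 19.97 |
| Dudley, Wolverhampton and SW Staffordshire | 3,325 | 0.60 | 1.32 |
| Total | 17,802 | p = 0.580 | 94.52 |

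- Between-service variance = 94.52 / 17,802 = 0.00531.
- R² = 0.00531 / (0.580 × 0.420) = 0.00531 / 0.2436 = 2.2%.
- SE ratio = √(1 − 0.0218) = 0.989, a reduction of about 1.1%.
- Gain in effective sample size = 1/(1 − 0.0218) − 1 = 2.2%, or about 400 of 17,802 women.

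**3. Adding status.** Missing: 24 + 5 + 2 = 31 of 17,802 (0.17%). Prevalent women under 60 number 5,619 (32%), and their share by service runs from 18% to 68%. The SAP gives no attendance by status, so the gap g between prevalent and other screens is assumed. With service means held fixed, the added R² is g² × (mean of f(1 − f)) / 0.2436. Here f is the prevalent share in each service, and the weighted mean of f(1 − f) is 0.194.

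| Assumed gap | Total R² | SE ratio | Effective sample size | Power, 3-point difference |
|---|---|---|---|---|
| Unadjusted | 0 | 1 | – | 78.0% |
| Service only | 2.2% | 0.989 | +2.2% | 78.9% |
| + status, 10 points | 3.0% | 0.985 | +3.1% | 79.3% |
| + status, 20 points | 5.4% | 0.973 | +5.7% | 80.2% |
| + status, 30 points | 9.4% | 0.952 | +10.3% | 81.9% |

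Power is for one pairwise comparison with 4,000 per arm on a 58% base. For a 2-point difference it rises from 44.4% to between 45.2% (service only) and 48.0% (30-point gap). Simulated robust Poisson fits gave SE ratios of 0.989 for service only, 0.974 at 20 points and 0.954 at 30 points, in line with the formula.

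**4. Against the second-letter contrasts.** The difference detectable with 80% power is (1.96 + 0.84) × √(2 × 0.2436 / 4,000) = 3.09 points unadjusted and 3.06 with service. If the 8-point effect acted only on an assumed 35% to 50% of women who miss the first invitation, the contrast would be 8 × 0.35 = 2.8 to 8 × 0.50 = 4.0 points. The lower end of that range is slightly below the detectable difference.

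**The case against.** The strongest reply is that nothing here is wrong. An arm-only comparison under digit-based allocation is valid, its standard error already allows for chance imbalance, and no imbalance by arm is documented. That stands: the point concerns efficiency only.

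The SAP also already has a stronger instrument for the second letter. Its Secondary analysis pools (TT+OT) against (TO+OO), about 8,000 women a side. This cuts the SE by 1 − √(1/2) = 29% relative to one pairwise test. For 3 points on a 58% base, power is about 95% even at a Bonferroni level of 2.5%. That stands too, and it limits what adjustment adds, although the pairwise tests remain in the primary sequence.

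A reader might infer that the second-letter effects are small. The SAP does not say so. Its only effect size is "an absolute 8% increase in participation with timed appointments compared to open invitations", and its Introduction calls a second timed letter effective. The range of 2.8 to 4.0 points is an inference from who receives the second letter.

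Finally, adding a missing category outright would conflict with the existing rule to impute status from age, and replacing the primary model after seeing results by arm would be a post hoc change. Both objections are accepted and shape the fix.

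**Conclusion.** The point holds as a minor improvement to a valid analysis. The gain the documents support is the one from service: about 1% of the SE, about 2% in effective sample size, and about one percentage point of power for a 3-point difference. Even this uses 2021/22 programme uptake in place of 90-day attendance in the study, and observed service sizes in place of planned ones.

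A reader might infer a gain worth about 10% more women. That needs a 30-point attendance gap for prevalent screens, and the SAP gives no gap at all. Over assumed gaps of 10 to 30 points, the total gain is about 1.5% to 5% of the SE. Nor do the documents support reading the unadjusted result as biased. With "we planned to evaluate 16,000 women in total (4,000 per arm"), the comparisons of the size used for planning are not in question.

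**What to change.** - Specify the primary model as arm + service + age_prev_status, keeping the robust variance, and use the same covariates in the pooled first-letter and second-letter contrasts.
- Handle missing status by the SAP's existing rule (impute from age). Keep a missing category only for women the rule cannot resolve; Supplementary Table 2 still shows 31 as missing.
- Report the unadjusted rate ratio beside the adjusted one as a sensitivity result.
- If results by arm are already known, leave the arm-only model as primary and present the adjusted model as a labelled supportive analysis.

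The cost is a sentence or two in the SAP, two factor variables in the Stata command, one more table column and slightly more analysis work. No new data are needed.

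### The primary 90-day attendance tests use a Poisson likelihood ratio that ignores the robust variance, so they are far too conservative and can contradict the confidence intervals the plan treats as equivalent

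*SAP*

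**What the plan says.** Under Primary endpoint methods, the SAP specifies Poisson regression "with number of subjects attending within 90 days of their first offered appointment as the outcome", "offset by total numbers invited". The arms are "compared using Poisson regression model with robust variance estimates to take account of clustering", and this robust variance supplies the 95% confidence intervals for the incidence-rate ratio (IRR). For significance the section turns to another tool: "A likelihood-ratio test is used to check the significance of the regression coefficient in the poisson regression model", with Stata's lrtest named. It closes by counting an IRR as significant when its 95% interval leaves out 1, and treats that as matching a p-value below 0.05.

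Under Primary analysis, "a global likelihood ratio test on 3 degrees of freedom will be applied to assess the significance of a difference" comes first. Five pairwise hypotheses follow in fixed order (TT v OO, TT v OT, TO v OT, TT v TO, OT v OO), and each is reached only if the one before it gave p below 0.05.

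Under Preparing data for analysis, the file is reshaped to one line per woman. Under Data linkage and variable derivation, 90dayattend is coded 1 or 0 for each woman.

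**The concern.** Robust variance is the usual repair when a Poisson model is fitted to a 0/1 outcome, and it does put the confidence interval right. A likelihood-ratio test compares two maximised likelihoods and never uses the robust variance, so its p-value keeps the Poisson assumption that the variance equals the mean. At the attendance rates expected here that assumption is badly wrong.

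Two things are at stake. The global test runs far below its nominal level. For the pairwise steps, the SAP offers a likelihood-ratio rule and a confidence-interval rule as if they were the same. Where they differ, one stops the fixed sequence and the other lets it go on, and nothing in the SAP says which governs. That leaves a confirmatory decision open once the data are known.

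**Working it through.** **Inputs.** Rates of 65% and 73%, 524 per group, 80% power, two-sided 5%, and 4,000 per arm are all from Sample Size Justification. The value 69% is the midpoint of the two rates. The value 55% is my assumption; it lies within the 42% to 67% service uptake in Supplementary Table 1. Differences of 2 to 5 points from 65% are an assumed range, because the SAP gives no expected difference for the individual steps. Women are treated as independent.

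**The SAP's own figure.** The pooled-variance formula for 65% v 73% gives 524 per group, with power 80.04%. The stated sample size reproduces.

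**Variance of the log IRR, n per arm.**
- Poisson likelihood: 1/(n p1) + 1/(n p2)
- Correct for a 0/1 outcome, and what the robust variance estimates: (1-p1)/(n p1) + (1-p2)/(n p2)

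With equal rates the first exceeds the second by 1/(1-p), about 3.2 at 69%.

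**True size of the nominal 5% two-arm likelihood-ratio test.** The statistic is deflated by (1-p), so the size is 2 × [1 - Φ(1.96/√(1-p))].
- p = 0.69: 1.96/√0.31 = 3.520, size 0.04%
- p = 0.65: 1.96/√0.35 = 3.313, size 0.09%
- p = 0.55: 1.96/√0.45 = 2.922, size 0.35%
- p = 0.42: 1.96/√0.58 = 2.574, size 1.0%

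For the global 3-df test, simulation at 4,000 per arm (400,000 replicates) gives a size below 0.01% at both 65% and 69%.

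**Power, worked for 65% v 68% at 4,000 per arm.**
- Log IRR = ln(0.68/0.65) = 0.04512
- Poisson SE = √(1/2600 + 1/2720) = 0.02743
- Correct SE = √(0.35/2600 + 0.32/2720) = 0.01588
- Poisson likelihood ratio: Φ[(0.04512 - 1.96 × 0.02743)/0.01588] = Φ(-0.544) = 29%
- Robust Wald: Φ[0.04512/0.01588 - 1.96] = Φ(0.881) = 81%

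**Range at 4,000 per arm**, by summing the exact binomial probabilities. The last column is the share of trials in which the robust interval excludes 1 while the likelihood-ratio p is at least 0.05.

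| Rates | Poisson LR | Robust Wald | Rules disagree |
| --- | --- | --- | --- |
| 65% v 67% | 7% | 47% | 40% |
| 65% v 68% | 29% | 81% | 52% |
| 65% v 69% | 65% | 97% | 31% |
| 65% v 70% | 91% | 99.8% | 9% |
| 65% v 73% | >99.9% | >99.9% | <0.01% |

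**The case against.** - **Planned power.** A reader might infer that the SAP's 80% power falls to about 24%. The arithmetic is right for 65% v 73% at 524 per group (23.6%), but that is not the size of any planned test. The SAP states that "524 persons per group would give 80% power to detect this difference as significant at 5% level with two-sided testing" in the context of its interest in subgroups, then plans 4,000 per arm. Subgroup analysis calls only for estimates with 95% intervals, and the Table 6 template has no p-value column. For the planned effect at the planned size, power stays above 99.9%. This objection stands, and the 24% is not part of the finding.
- **Data layout.** A reader might also infer that the model will be fitted to four arm totals. It would then be saturated, and the robust standard errors would collapse to zero. The data-preparation sections build one row per woman with a 0/1 outcome, and on that file the collapse does not arise. What remains is that the phrase "offset by total numbers invited" does not fit that file.
- **Source of the pairwise p-values.** It would go too far to say that these certainly come from lrtest. The interval sentence supports the other reading, under which the pairwise decisions have the right size. The text contradicts itself rather than settling the matter. The global test is unambiguously a likelihood-ratio test.
- **Consequence.** The error cannot inflate false positives. The Table 4 template shows the IRR and interval for all five contrasts, and the best arm is reported regardless of significance. This stands and limits the harm to the confirmatory tests.

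**Conclusion.** The concern holds in this form: the global test and the named coefficient test use a likelihood that is wrong for a yes/no outcome, and the claimed match between interval and p-value is untrue if the p-value comes from lrtest. The two-arm test's true size is about 0.04% to 0.35% over 69% to 55% attendance, against a nominal 5%.

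The practical loss at 4,000 per arm falls on differences of roughly 2 to 4 points. It is small at 5 points and negligible at the SAP's 8 points. Differences of that size are plausible at the later steps, which compare intermediate strategies, but this is an assumption that the SAP neither states nor rules out. The power figures assume independent women, equal arms and a base rate of 65%. The mechanism needs none of these, only attendance that is not rare.

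**What to change.** Under Primary endpoint methods, state that the model is fitted to the one-row-per-woman file with 90dayattend (0/1) as outcome, and delete the offset phrase. Replace the lrtest sentence, and the matching wording under Primary analysis, with Wald tests from the same robust covariance matrix that gives the intervals: testparm for the global 3-df test, and lincom or pwcompare for the five pairwise steps. The sentence equating interval and p-value then becomes true for the pairwise comparisons and can stay.

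The alternative is to take every likelihood-ratio test from a binomial likelihood, make that the only decision rule, and drop the sentence equating it with the robust interval.

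The cost is two sentences of SAP text and a different post-estimation command. No new data are needed. The list of changes puts the end of the analysis at 3 May 2024, so it should also record which test produced any p-values already calculated.

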### Data linkage and variable derivation

The following variables are derived based on the source data.

| Variable | Definition | Notes |
| --- | --- | --- |
| *service* | Screening service | - Derived from service of which each data was extracted from: - 1, Central and East London (pilot area). - 2, Outer Northeast London. - 3, North London. - 4, Cambridge. - 5, North and East Devon. - 6, Doncaster. - 7, Dudley, Wolverhampton and Southwest Staffordshire, and - 8, East Lancashire. |
| *appointmenttag* | Tag each appointment, in the chronological order of appointment date. | Derived from *date*, labelled 1, 2, 3, etc by the chorological order of each appointment offered/ booked.  For reshaping data between wide and long format, each line represents either an appointment or per woman. |
| *flagadminerror* | Flag for administrative errors that wrong type of invitation letter was sent. | Derived from *flag2oiinviteandnotaoicl* and *flag3tabutanoiletterused.*   - 1, if Y on either variable above, error. - 0, otherwise, no error.   Should be a very small proportion of the sample. |
| *90dayattend* | Primary endpoint, 90-day attendance since first offered appointment | Derived from *attendedappointment and date*.   - 1, if Y on *attendedappointment* and the difference between variable screeningdate and variable *date* is less than or equal to 90 days. - 0, if N on *attendedappointment*, or attended but the difference between variable screeningdate and variable date is greater than 90 days: |
| *180_survtime* | Follow-up duration | - If Y on *attendedappointment, then t*he number of days between variable *screeningdate* and variable *date* if it is less than or equal to 180 days. - Otherwise, then *t*he number of days between variable *date* and the 31^st^ of January 2024 or the end of 180-day follow-up, whichever is the first.   As the time of event/censoring time in cox regression. |
| *180dayattend* | Secondary endpoint, 180-day attendance since first offered appointment | - 1, if Y on *attendedappointment* and the difference between variable *screeningdate* and variable *date* is less than or equal to 180 days, or to the 31^st^ of January 2024, whichever is the first. - 0, if N on *attendedappointment*, or attended but the difference between variable screeningdate and variable date is greater than 180 days.   This is the event variable for cox regression. |

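### The Poisson likelihood-ratio test named for yes/no attendance ignores the robust variance, runs far below its 5% level and can contradict the robust confidence interval

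*SAP*

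**What the plan says.** The outcome is "Primary endpoint, 90-day attendance since first offered appointment", coded 1 or 0 for each woman (SAP, Data linkage and variable derivation).

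Under Primary endpoint methods it is modelled by Poisson regression offset by the number invited, with vce(robust), and a 95% CI for the incidence-rate ratio (IRR) is reported. On testing, the same section says: "A likelihood-ratio test is used to check the significance of the regression coefficient in the poisson regression model", and names Stata's lrtest. It then calls an IRR significant when the 95% CI excludes 1, "which is analogue to the p-value is smaller than 0.05".

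Under Primary analysis, "a global likelihood ratio test on 3 degrees of freedom will be applied to assess the significance of a difference" among the four arms. Five pairwise hypotheses follow in fixed order: TT vs OO, TT vs OT, TO vs OT, TT vs TO, OT vs OO. Each is tested only if the one before it was rejected at p<0.05. The Table 4 template prints IRR, CI and p-value side by side.

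Sample Size Justification says: "For a comparison of two groups with participation rates of 65% and 73%, 524 persons per group would give 80% power", two-sided at 5%, and then "we planned to evaluate 16,000 women in total (4,000 per arm").

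**The concern.** A 0/1 outcome with attendance p has variance p(1−p). The Poisson likelihood takes the variance to be p. The sandwich variance repairs this for the confidence interval, but an LR statistic is built from the two log-likelihoods alone and never sees the sandwich variance. Interval and test therefore rest on different variances, although the SAP treats them as interchangeable.

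What is at stake is the ordered sequence. If LR p-values open each step, a real difference that the CI shows can fail its test, close every later hypothesis and be reported as no difference between letter strategies. Table 4 could then show a CI excluding 1 beside p>0.05, with no rule for which one counts.

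**Working it through.** **Inputs from the SAP.** Rates 65% and 73%, 524 per group, 4,000 per arm, two-sided 5% (Sample Size Justification). Service uptake of 42% to 67% in 2021/22 (Supplementary Table 1); the simple mean of the seven services is (42+54+58+60+61+63+67)/7 = 57.9%, taken as 58%. The robust test is assumed to come from a fit with one row per woman.

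**1. The plan's own figure.** With the pooled-variance two-proportion formula and mean rate 0.69,

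n = [1.960·√(2·0.69·0.31) + 0.842·√(0.65·0.35 + 0.73·0.27)]² / 0.08² = 523.5, rounded up to 524.

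This reproduces the SAP (power 80.0%). The planning calculation therefore used the binomial variance.

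**2. Size of the Poisson LR test.** Under no difference the LR statistic behaves as (1−p)·χ². The true 1-df size is P(χ²₁ > 3.841/(1−p)) and the 3-df size is P(χ²₃ > 7.815/(1−p)).

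| Attendance p | 3.841/(1−p) | 1-df size | 3-df size |
|---|---|---|---|
| 42% | 6.62 | 1.0% | 0.37% |
| 58% | 9.15 | 0.25% | 0.033% |
| 65% | 10.98 | 0.09% | 0.006% |
| 69% | 12.39 | 0.04% | 0.001% |
| 73% | 14.23 | 0.016% | 0.0002% |

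Simulation with 400,000 trials per setting agrees. At 4,000 per arm the robust Wald test has size 4.9–5.0% at rates of 65–73%. The LR p-value is the same from aggregated counts with an offset as from individual rows, so the data layout does not cure it.

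**3. A worked conflict.** Take 2,520/4,000 against 2,400/4,000; the pooled rate is 0.615.

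- LR = 2·[2,520·ln(0.63/0.615) + 2,400·ln(0.60/0.615)] = 2.93, p = 0.087.
- Robust SE of ln(IRR) = √(1/2,520 − 1/4,000 + 1/2,400 − 1/4,000) = 0.0177. IRR = 1.05, 95% CI 1.014–1.087, Wald χ² = 7.59, p = 0.006.
- The ratio 2.93/7.59 = 0.39 matches 1 − 0.615, as the theory predicts.

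With 4,000 per arm the CI begins to exclude 1 at an observed difference of about 2.1 points. LR reaches p<0.05 only at about 3.4–3.5 points from a 60% base and 3.6 points from a 65% base. Between these limits the two rules disagree. In all simulated trials the conflict was a CI excluding 1 with a non-significant LR test, never the reverse.

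**4. Power at 4,000 per arm.**

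| True rates | Poisson LR | Robust Wald |
|---|---|---|
| 65% vs 73% | >99.9% | >99.9% |
| 65% vs 69% | 65% | 97% |
| 65% vs 68% | 29% | 81% |

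**5. The ordered sequence.** The SAP gives no separate effects for the first and second letter, so these are assumptions: additive effects on a 65% base, 4,000 per arm. The table gives the probability that all of steps 1 to 4 (through TT vs TO) are rejected.

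| First / second letter (points) | Poisson LR | Robust Wald |
|---|---|---|
| 5.5 / 2.5 | 0.6% | 54% |
| 8 / 3 | 16% | 87% |
| 8 / 4 | 29% | 96% |

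**6. The planning scenario under the named test.** At 524 per group and 65% vs 73%, LR power is 24% against 80% for robust Wald. LR would need about 1,275 per group for 80%.

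**The case against.** **The source of the p-values is not explicit.** Primary analysis names LR only for the global test; the ordered hypotheses need only p<0.05. Primary endpoint methods also contains a CI rule, and the Table 4 footnote does not name a test. This stands in part. LR is the plain reading because no other test is named for the coefficients, but the defect is best described as two rules that can disagree, with neither put in charge.

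**The main comparison is safe.** This stands. An 8-point TT vs OO difference is detected almost surely by either test. The error is conservative, and the IRRs and robust CIs are unaffected. The SAP also reports the most successful arm whatever the tests show.

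**Stronger readings that the SAP does not support.** A reader might infer that the trial's power falls from 80% to 24%. It does not: 524 is a building block for the planned size, the arms hold 4,000, and Subgroup analysis plans estimates with CIs and no tests. A reader might also infer that every later step loses most of its power. That fails too: with effects of 5.5 and 2.5 points, TT vs OT keeps 96% power under LR (against more than 99.9%), while TO vs OT falls to 27% (against 83%). The 0.6% chain figure is the worst of the three scenarios shown and should not be quoted alone.

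**The conflict depends on a per-woman fit.** True for the robust CI. The SAP describes counts with an offset, but it also restructures the data to one line per woman and codes the outcome for each woman.

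**Conclusion.** The concern holds in this limited form. The Poisson LR test named for the primary endpoint does not have its stated 5% level, and the SAP's equation of CI and p-value is false for the two methods it names. The damage falls on moderate differences, with observed gaps of roughly 2.1 to 3.6 points at 4,000 per arm, in the later steps of the sequence, where one false non-rejection ends testing. There is no inflation of false positives. The named test is also not the two-proportion test behind the sample size.

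The size figures depend only on the attendance rate. The power figures assume the stated true rates, and the chain figures assume additive letter effects that the SAP does not give. It should be corrected because it governs the primary inference.

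**What to change.** In Primary analysis and Primary endpoint methods, replace the likelihood-ratio test with Wald tests from the robust variance of the Poisson model fitted to one row per woman: a 3-df joint test of the arm terms for the global test, and 1-df contrasts for the five ordered pairs. Alternatively, take the LR tests from a binomial model and keep the IRR and robust CI for estimation.

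State that these p-values drive the hierarchy, and say that the model is fitted per woman. Use the same method for the two 90-day contrasts under Secondary analysis, where no test is named.

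With the Wald option each unadjusted p-value agrees with its CI, the size returns to about 5%, and the planned 80% at 524 per group is recovered. The binomial LR option also restores the level, but its p-value may differ slightly from the robust CI at the margin. The cost is a few sentences and a few lines of code. No new data are needed.
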